
### Safety data

Adverse events will be tabulated by allocated treatment group; no formal comparisons will be made. Adverse events that meet the serious criteria (that is they (a) resulted in death, (b) were life threatening, (c) resulted in persistent or significant disability or incapacity, (d) prolonged an ongoing hospitalization or (e) resulted in hospitalization) will be identified (as serious adverse events) and all events will be divided into ‘expected’ events listed in the study protocol and other ‘unexpected’ events. Unexpected events will be independently coded by at least two trained research nurses blinded to treatment allocation using the Medical Dictionary for Regulatory Activities [17]. Any discrepancies between nurses in classification will be resolved by a cardiac surgeon also blinded to treatment allocation. System organ class terms will be used to group events, with groupings further broken down into preferred terms if necessary.

### Meta-analysis

It is intended to perform a meta-analysis combining the primary outcome results from this study with any previous systematic reviews and studies. This analysis will be performed using standard meta-analysis methods for binary outcomes, using a random effects model. Previous studies will be included in the meta-analysis if they fulfil the following criteria: (a) the patient population was patients undergoing cardiac surgery, (b) restrictive and liberal RBC transfusion strategies are compared, although the actual haemoglobin concentration and haematocrit thresholds for transfusion may differ between studies, (c) the outcomes included in the meta-analysis are postoperative morbidity or mortality.

### Pre-specified ancillary analyses

There are three pre-specified ancillary observational analyses in the study protocol:Estimating the relationship between the number of RBC units transfused, and the risk of the primary outcome or death from any cause, stratified by trial arm.Investigating the relationship between percentage decline in haemoglobin concentration from the preoperative level and the risk of primary outcome or death from any cause, taking into account the number of RBC units transfused.Investigating whether the age of the RBCs is associated with the risk of primary outcome or death from any cause.

To address analyses (a) and (b), three logistic regression models will be fitted with the following explanatory variables:Total number of RBC units transfused (either pre- or post-randomization)Percentage decline in haemoglobin concentration from the preoperative levelTotal number of RBC units transfused and percentage decline in haemoglobin concentration.

To address analysis (c), the age of the ‘oldest’ unit of RBCs received by a patient will be fitted as an explanatory variable. The age will be determined by linking the donation numbers of all RBCs transfused to a blood bank database and retrieving the date of donation.

In all of these models, adjustment will be performed for any variables found to be potential confounders, defined as: variables associated with both the exposure and the outcome that are not an intermediary step on the causal pathway between the exposure and outcome, that significantly contribute to the relevant multivariable model (defined as a likelihood ratio *P* value <0.05 or by modifying the effect estimate by greater than 10%). In analyses (a) and (b), the following variables have been identified as possible confounders: randomized allocation, operation type, centre (as a random effect), EuroSCORE, age and sex. Likewise for analysis (c), number of RBC units transfused, blood group, EuroSCORE, age and sex have been identified. For analyses (a) and (b), the instrumental variable method of controlling for confounding will also be explored, using randomized allocation as the instrumental variable [18].

Some potential issues have been identified. It may be sensible to restrict the analyses to include only patients who did not receive a proportionately large number of RBC units (for example, restrict the analysis to include those who received ten units or fewer). This approach would be used if, for example, the data obtained from patients who received large numbers of RBC units resulted in outliers and caused models not to fit adequately.

In all of the analyses (with the exception of decline in haemoglobin concentration) there is a potential problem that some of the RBCs might be transfused after a primary outcome event. Therefore fitting these models might not be appropriate, owing to the timing of the exposure relative to the outcome event. If this proves to be the case (for example, a non-negligible number of RBC units are given after the primary outcome measure or effect estimates do not make sense), alternative approaches will be considered [19], including:Nested matched case-control study: each patient experiencing a primary outcome event (‘cases’) will be matched to a ‘control’ (by matching on at least centre and randomized allocation); other factors (for example, operation type) may also be used if sufficient matched controls are available). For both the ‘case’ and the ‘control’, any RBC units transfused after the time that the case first experienced the primary outcome will be excluded from analyses.Time-to-event analyses with a time varying covariate of RBC units given: this would address the issue of exposure time (for ‘cases’, the event would be the primary outcome event, and for controls the last follow-up), but would ignore any blood given after the occurrence of a primary outcome event (that is, RBC units will only be excluded for ‘cases’).

For analysis (c), defining the age of the blood as the age of the oldest unit of blood transfused is likely to be confounded by the number of RBC units transfused. Therefore, the sensitivity of the results of this analysis will be explored by refitting the model using other definitions of the exposure variable, possibly including: the mean age of all RBC units, the use of any blood more than 14 days old (yes or no), the number or percentage of RBC units given that are more than 14 days old, the use of blood that is older than the median age of all RBC units transfused (yes or no). There are also potential problems with all of these approaches, for example, the use of any blood more than 14 days old is likely to be confounded by blood group and many of the methods that dichotomize patients into older versus younger blood will either need to exclude patients not transfused any RBC units, or to fit as a three-level variable of older blood, younger blood or no blood, which may in turn cause problems with interpretability.

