### Sample size

Based on previous data [1] and allowing for anticipated non-adherence to the allocated thresholds [7], the primary outcome frequencies were hypothesized to be 17% and 11% in the liberal and restrictive groups. A sample size of 1,468 was required to detect this difference with 90% power and 5% significance (two-sided test). The target sample size was inflated to 2,000 to allow for uncertainty about non-adherence, since higher than expected non-adherence would reduce power. Full details are reported elsewhere [7].

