### Adjustment in models

The intention is to adjust all models for factors included in the cohort minimization: operation type (four different types) as a fixed effect and centre (17 different centres) as a random effect (or a shared frailty term in time-to-event models). Occasionally, the operation type might differ between the study database and the randomization system because it has been entered incorrectly into the randomization system. In this case, the value from the study database will be used, as the operation type recorded on the database will have been confirmed to be correct in such instances. For all treatment comparisons, the liberal group will be the reference group.

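### A data-driven screen decides whether pre-named confounders stay in the ancillary models, so number of RBC units can drop out of the blood-age analysis; centre and operation type are not on that analysis's list

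*SAP article*

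**What the plan says.** All of this is in the SAP article.

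- **Rule (Pre-specified ancillary analyses).** "In all of these models, adjustment will be performed for any variables found to be potential confounders". A variable must be associated with exposure and outcome, must not lie on the causal pathway, and must be one of those "that significantly contribute to the relevant multivariable model (defined as a likelihood ratio" P value below 0.05, or must qualify "by modifying the effect estimate by greater than 10" per cent. The scale of the change (odds ratio or log odds ratio) and the order of selection are not given.
- **Candidates for (a) units transfused and (b) haemoglobin decline.** Variables "identified as possible confounders: randomized allocation, operation type, centre (as a random effect), EuroSCORE, age and sex".
- **Candidates for (c) age of blood.** "Likewise for analysis (c), number of RBC units transfused, blood group, EuroSCORE, age and sex have been identified".
- **Known problem in (c).** The same section says that age of the oldest unit "is likely to be confounded by the number of RBC units transfused". Its response is to refit with other definitions of the exposure.
- **General rule (Adjustment in models).** "The intention is to adjust all models for factors included in the cohort minimization", namely operation type as a fixed effect and centre as a random effect.

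**The concern.** The ancillary analyses estimate the association of a non-randomized exposure with outcome, so they stand or fall on the adjustment set. The plan names a short list on subject-matter grounds and then lets the trial data decide which members stay.

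Two consequences follow. A real confounder with a modest outcome association can fail the screen, and several such omissions can add up. The confidence interval from the selected model is then computed as if that model had been fixed in advance.

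The case that matters most is number of RBC units in (c). The age of the oldest of several units can only stay the same or rise as units are added, so this exposure partly measures how much blood a patient received. Without number of units in the model, an apparent effect of old blood may simply be an effect of heavy transfusion.

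**Working it through.** **1. What is guaranteed to be in each model.** The rule covers all the ancillary models, and the named variables are called possible confounders, that is, candidates for it. No sentence exempts any of them. The further requirement of association with both exposure and outcome makes omission easier.

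**2. Centre and operation type.**
- For (a) and (b), both are candidates and can be screened out.
- For (c), neither is a candidate. They are absent because they are not listed, not because of the screen.
- Adjustment in models refers to all models and exempts none.
- The fallback nested case-control design is offered for every analysis except haemoglobin decline, so it covers (c). It matches on at least centre and randomized allocation. Centre is thus a minimum requirement in the fallback for (c) but is not listed for its main model.

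**3. What the 10% limb can miss by itself.** Suppose adjustment multiplies the odds ratio by 0.901, a 9.9% fall. The share of the log odds ratio removed is 1 − ln(0.901 × OR)/ln(OR):

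| Before | After | Share of log OR removed |
|---|---|---|
| 1.20 | 1.08 | 57% |
| 1.15 | 1.04 | 75% |
| 1.10 | 0.99 | all of it |

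If the 10% were meant on the log scale, 1.20 could fall only to exp(0.9 × ln 1.20) = 1.18 without being flagged. The unstated scale therefore changes the rule materially.

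**4. How far the P value limb rescues this.** I simulated one confounder that takes the odds ratio per unit from about 1.20 to 1.08. The inputs are assumed, not taken from the plan: n = 2,000, 300 runs per setting, event rate mostly about 13% to 16%. Share of runs in which both limbs fail, so that the confounder is dropped:

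| Exposure SD (units) | Correlation 0.3 | 0.5 | 0.7 |
|---|---|---|---|
| 1 | 0% | about 20% | 50% |
| 2 | 0% | under 1% | 9% |
| 3 | 0% | 0% | under 1% |

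A single strong confounder is usually kept. The losses in step 3 arise mainly with a narrow exposure range and high correlation.

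**5. Several modest confounders together.** A second simulation, also on assumed inputs, used n = 2,000, five true confounders each with log OR 0.10 to 0.15 per SD, each correlated 0.2 to 0.4 with the exposure, 400 runs per scenario, the 10% taken on the odds ratio scale, and backward elimination (the plan states no procedure). At least one true confounder was dropped in 81% to 99% of runs. Coverage of the 95% interval was 42% to 88%, against 93% to 95% with all five forced in. Mean bias was 0.03 to 0.11 in log OR. The 42% comes from correlation 0.4, where the confounders explain 5 × 0.4² = 80% of the exposure variance, an extreme case. At correlation 0.2 (5 × 0.2² = 20%), coverage was 85% to 88%.

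**6. Is there room to force the variables in?** The Sample size section says that "the primary outcome frequencies were hypothesized to be 17% and 11% in the liberal and restrictive groups". With 1,000 per arm this gives 170 + 110 = 280 patients with a primary outcome event. The ancillary endpoint is the primary outcome or death, so its count would be no lower at these rates.
- A model for (a) or (b) with one exposure, operation type (four types, three terms), EuroSCORE, age and sex entered linearly, and a centre variance has 1 + 3 + 3 + 1 = 8 parameters, or 280/8 = 35 events per parameter.
- If (a) is fitted separately by arm, this becomes 170/8 ≈ 21 and 110/8 ≈ 14.
- For (c), no count can be given. It may exclude untransfused patients, and the coding of blood group is not stated.

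**The case against.** **The plan already guards against confounding.** It adds an instrumental-variable analysis for (a) and (b), a matched fallback design and alternative exposure definitions for (c). This stands in part: reliance on any one selected model is reduced. None of it secures adjustment in the main models, however, and the instrumental-variable analysis does not extend to (c).

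**The rule has two limbs.** A reader might infer from the table in step 3 that the plan would overlook 57% to 100% of an effect. The documents do not support that. The figures test the 10% limb alone, and the P value limb would retain many such confounders (step 4).

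**The general adjustment rule may not reach these models.** A reader might infer an outright contradiction over centre and operation type. That is arguable. Adjustment in models states an intention and closes on treatment comparisons. Missing predictor data, in the same general block, describes all other predictors as preoperative values of longitudinal outcomes, which does not fit EuroSCORE, blood group or RBC units. The block reads mainly as covering the randomized outcome models. A gap remains on either reading: if the rule applies, centre and operation type cannot be screened candidates in (a) and (b); if it does not, (c) lacks both.

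**Forcing everything in would be wrong.** This stands. The list for (a) and (b) includes randomized allocation, but (a) is described as stratified by arm, and allocation is the instrument for both analyses. Forcing a valid instrument into the conventional model can amplify residual confounding.

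**Conclusion.** The point holds in a limited form. The screen leaves the final adjustment set unknown until the data are seen, allows number of RBC units to be dropped from (c) against the plan's own reasoning, and yields intervals that ignore selection. The omission of centre and operation type from (c) needs either correction or a sentence of explanation.

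The size of the bias cannot be fixed from the documents. The simulations show direction and a wide range, and rest on assumed confounder strengths, correlations and selection order. Nor should a reader conclude that precision never argues for a shorter model: the 280 events are for the primary outcome across both arms, and (c) may have fewer.

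This is a minor point. It concerns analyses labelled observational and leaves the randomized primary and secondary comparisons untouched.

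**What to change.** - **(a) and (b):** enter operation type, centre (random effect), EuroSCORE, age and sex regardless of P value or change in estimate.
- **(c):** enter blood group, EuroSCORE, age and sex in the same way. Always keep number of RBC units where oldest-unit age is the exposure. Add centre and operation type, or state why the general adjustment rule does not apply.
- **Randomized allocation:** handle it through the stated stratification by arm and the instrumental-variable analysis, not by blanket forced entry.
- **Screen:** keep it only for additional variables, and state the scale of the 10% change and the order of selection.

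The cost is a change of wording and fewer modelling steps. The downside is a few more parameters: adding centre and operation type to (c) costs three fixed terms and one variance, which matters most if untransfused patients are excluded. The Discussion says that the plan has since been executed, so the practical step may be to report the fully adjusted models alongside any selected ones.

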## Methods and Design

TITRe2 is a multicentre, UK-wide, open parallel group randomized controlled trial. It is the largest randomized controlled trial to date (2,000 randomized patients) to compare RBC transfusion strategies following cardiac surgery. Patients are randomized in a 1:1 ratio to one of two RBC transfusion strategies: (a) a ‘restrictive’ threshold, whereby transfusions are given if the haemoglobin concentration is below 7.5 g/dl (or haematocrit <22%), or (b) a ‘liberal’ threshold, whereby transfusions are given if the haemoglobin concentration is below 9 g/dl (or haematocrit <27%). Cohort minimization is used to minimize imbalance of: (a) centre and (b) operation type. The study population is all adult patients (aged 16 or over) undergoing non-emergency elective cardiac surgery (this includes non-emergency cases admitted from home and non-emergency inpatient cases). Eligibility criteria are as inclusive as possible, to promote the applicability of the evidence obtained during the trial. Full details of the study background and design have been reported elsewhere [7].

Following recommendations from the International Conference on Harmonisation of Technical Requirements for Registration of Pharmaceuticals for Human Use [8], a pre-specified detailed statistical analysis plan has been written prior to database lock and final analysis of the trial data. However, during the course of the study, analysis requested by the Data Monitoring and Safety Committee has been performed prior to finalization of this statistical analysis plan. This analysis comprised monitoring of recruitment rates and data completeness, monitoring of demographic data, and descriptive comparisons of safety data, including the primary outcome measure, by masked treatment allocation. At a pre-planned interim analysis carried out after half the participants had been followed up, a formal comparison was performed for the primary outcome measure only. No formal comparisons were performed at any other time.

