**Flow of participants.**

Participants consent to the study before surgery if they meet all of the pre-consent eligibility criteria (see Figure 1) and give written consent. They are then randomized if at any point post-surgery they meet the post-consent eligibility criteria (haemoglobin concentration falls below 9 g/dl or haematocrit below 27%). This means that a significant proportion of patients (estimated to be approximately 30% from earlier studies [1]) consent to the study but are not randomized. Randomized patients should be given a RBC transfusion as soon as possible after haemoglobin or haematocrit levels breach the relevant thresholds, and at most within 24 hours.

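### Ancillary analysis (b) does not name preoperative haemoglobin as a covariate; if low preoperative haemoglobin carries its own risk, larger percentage declines can look protective when they have no effect

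*SAP article*

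**What the plan says.** In the SAP article, under Pre-specified ancillary analyses, analysis (b) takes as its exposure the "percentage decline in haemoglobin concentration from the preoperative level". Three logistic models serve analyses (a) and (b): total red cell (RBC) units, percentage decline, and both together.

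On covariates, "the following variables have been identified as possible confounders: randomized allocation, operation type, centre (as a random effect), EuroSCORE, age and sex". The same paragraph gives a general rule. A variable is adjusted for if it is associated with exposure and outcome, is not on the causal pathway, and either has a likelihood ratio P value below 0.05 or changes the estimate by more than 10%. An instrumental-variable analysis with allocation as the instrument will also be explored.

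On who is analysed, the text under Flow of participants says of consented patients: "They are then randomized if at any point post-surgery they meet the post-consent eligibility criteria (haemoglobin concentration falls below 9 g/dl", or haematocrit below 27%. Patient population restricts all study analyses to randomized patients. Under Methods and Design, the strategies then transfuse below 9 g/dl (liberal) or 7.5 g/dl (restrictive).

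**The concern.** Percentage decline is a ratio of two measurements. Design restricts one of them: the postoperative value has to fall below an entry threshold, and transfusion then limits how far it drops. The other, preoperative Hb, is free to vary. Patients with large declines will therefore tend to be those who were not anaemic before surgery, and patients with small declines those who were.

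If preoperative anaemia is itself a marker of risk, a model without preoperative Hb credits the decline with the advantage of a good starting value. The result could be reported as larger falls in Hb being harmless or protective, in a trial about safe Hb levels. Preoperative Hb precedes the exposure and is needed to compute it, so it is neither an intermediary nor an extra data item.

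**Working it through.** **The plan's own figure.** The SAP gives no figure for analysis (b). Its sample size statement supplies the scale for the simulation: "the primary outcome frequencies were hypothesized to be 17% and 11% in the liberal and restrictive groups". The stated total of 1,468 is reproduced by the pooled two-proportion formula with continuity correction (1,402 without it):

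- n = [1.960√(2×0.14×0.86) + 1.282√(0.17×0.83 + 0.11×0.89)]² / 0.06² ≈ 701 per group.
- Corrected: (701/4)×[1 + √(1 + 4/(701×0.06))]² ≈ 734 per group, or 1,468 in all.

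The simulation below uses about 2,000 patients (the target) and an event rate of 14%, the midpoint of 17% and 11%.

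**Step 1: arithmetic of the exposure.** Let B be preoperative and P postoperative Hb. Decline D = 100×(1 − P/B).

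- Entry on Hb from B = 15 requires D above (15 − 9)/15 = 40%. From B = 11 it requires only D above (11 − 9)/11 = 18.2%.
- At P = 8.5, D is 15.0%, 29.2%, 39.3% and 43.3% for B = 10, 12, 14 and 15: a spread of 28 points from the starting value alone.
- At B = 13, moving P from 9 to 7.5 changes D from 30.8% to 42.3%, about 12 points.

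**Step 2: share of variance.** Near B = 13 and P = 8.5, D rises by 100P/B² = 5.03 points per 1 g/dl of B and falls by 100/B = 7.69 points per 1 g/dl of P. If P is unrelated to B, the share of the variance of D due to B is (5.03·SD_B)² / [(5.03·SD_B)² + (7.69·SD_P)²]. With assumed SD_B = 1.41 and SD_P = 0.40, 0.55 or 0.72, this gives 0.84, 0.74 or 0.62. Simulation at the same SDs gave 0.83, 0.71 and 0.59.

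The share falls when P tracks B: 0.46-0.67 with a moderate relation and 0.30-0.39 with a strong one (arms pooled). By arm, a simulation holding Hb near the allocated threshold (preoperative SD 1.2-1.8 g/dl around 13.3, natural fall 4.3, SD 1.3) gave 79-86% in the liberal arm and 31-52% in the restrictive arm. A further run put the restrictive arm at 27-50%.

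**Step 3: size of the bias by hand.** Take a true effect of zero and a share of 0.71. Ten points of D then correspond to 10×0.71/5.03 = 1.41 g/dl of B. If the odds are multiplied by g per 1 g/dl lower B, the apparent odds ratio (OR) per 10 points is about exp(−1.41×ln g): 0.87, 0.77 and 0.69 for g = 1.1, 1.2 and 1.3.

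**Step 4: simulation of the logistic model.** The true effect of decline is nil, with 150 replicates per setting. Covariates were allocation, a EuroSCORE-like score, age and sex.

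| Assumed odds per 1 g/dl lower B | OR per 10 points, without B | OR per 10 points, with B |
|---|---|---|
| 1.0 | 1.01 | 1.01 |
| 1.1 | 0.90 | 1.00 |
| 1.2 | 0.79-0.80 | 0.99-1.00 |
| 1.3 | 0.73 | 1.02 |

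Across the grid of assumed SDs and relations at odds of 1.2, the OR without B was 0.75-0.87 and falsely significant in 37-84% of replicates. With B it was 0.97-1.04, significant in 1-8%. The arm-specific simulation of Step 2 gave 0.87, 0.78 and 0.69 for odds of 1.1, 1.2 and 1.3 without B, and 0.97-1.02 with it.

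When a lower P was made truly harmful (OR 1.2 per 1 g/dl), with odds of 1.2 for B, the decline OR was 0.86 without B and 1.23 with it. The sign can reverse.

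**The case against.** **The general rule may already cover it.** The listed variables are described as possible confounders, and nothing says the list is closed. In the settings above, adding preoperative Hb moves the OR by at least 11% (0.87 to 0.97), so the 10% criterion would admit it if it were examined. This stands in part: adjustment is not ruled out. But the rule acts only on variables someone tests, and the identified list leaves this one out. Nor is the list a detail left to the protocol, since Changes to the original analysis plan counts the ancillary methods among this plan's own additions.

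**The inputs are assumed.** This stands. The document gives no Hb means, SDs or risk gradient, and does not define the postoperative value used for the decline.

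**Adjustment changes the question.** At a given preoperative Hb, decline is a linear function of postoperative Hb, so the adjusted estimate concerns postoperative Hb among patients with the same start. This is a real change of reading and should be stated. It is also the only comparison that separates the fall from the starting point.

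**The instrumental-variable option.** It is only to be explored, and it does not solve this for decline, because allocation also acts through the units transfused.

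**A stronger reading on timing.** From "In all of the analyses (with the exception of decline in haemoglobin concentration) there is a potential problem", a reader might infer that the plan wrongly treats Hb decline as free of reverse causation. The document does not support that. The sentence concerns RBC units given after an outcome event, and a decline-only model contains no units. Nor does any section say that the decline runs to the lowest Hb of the stay, so an effect of post-event values cannot be shown.

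**Conclusion.** The point holds in a conditional form. The named candidates for analysis (b) omit the denominator of the exposure, in a population whose postoperative Hb is restricted by design. If lower preoperative Hb raises risk beyond EuroSCORE, age and sex, a model limited to the listed covariates can show an OR per 10 points of decline of about 0.9 to 0.7 where the truth is 1, for assumed odds of 1.1 to 1.3 per 1 g/dl. Without that gradient there is no bias.

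A reader might go further and say that decline is merely preoperative Hb under another name, or that its sign can never be interpreted. That is too strong. In the restrictive arm roughly half or more of the variance comes from elsewhere, the pooled share falls to 0.30-0.39 if postoperative tracks preoperative Hb strongly, and entry is also possible on haematocrit alone.

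The correction is worth making because it is cheap and removes the bias. It concerns an ancillary observational analysis and does not touch the primary outcome or any randomized comparison.

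**What to change.** In Pre-specified ancillary analyses, name preoperative Hb as a mandatory covariate, exempt from the P value and 10% selection rule, in both models that contain percentage decline (decline alone, and decline with RBC units). Equivalently, replace the percentage by two terms: preoperative Hb, and the postoperative Hb from which the decline is computed. State that the estimate is the association with decline at a given preoperative Hb. The timing sentence needs no change on this account.

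The Discussion says the plan has since been executed, so any reported result of analysis (b) should be accompanied by the adjusted model, labelled as an addition.

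The cost is a line of text and one covariate already collected. The interval for decline will widen, mainly in the liberal arm, where little information about decline is independent of the starting value.

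### The ancillary models for red-cell units and age of blood count transfusions given after the event by default, and leave that default partly on how the estimate looks

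*SAP article*

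**What the plan says.** All of this is in the SAP article, section Pre-specified ancillary analyses.

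- **Outcome.** Each of the three analyses, (a) units, (b) percentage haemoglobin decline and (c) age of red cells, concerns the risk of the primary outcome or death from any cause.
- **Default models.** For (a) and (b), "three logistic regression models will be fitted with the following explanatory variables": units, haemoglobin decline, and both together. The units variable is "Total number of RBC units transfused (either pre- or post-randomization". For (c) the exposure is the age of the oldest unit received. Neither exposure stops at the event.
- **Acknowledged problem.** For everything except haemoglobin decline, "there is a potential problem that some of the RBCs might be transfused after a primary outcome event".
- **Trigger and response.** The plan would leave the default if, for example, "a non-negligible number of RBC units are given after the primary outcome measure or effect estimates do not make sense". In that case "alternative approaches will be considered".
- **Fallbacks.** One is a nested matched case-control study in which "any RBC units transfused after the time that the case first experienced the primary outcome will be excluded from analyses". The other is a time-to-event analysis with units as a time-varying covariate, where for cases "the event would be the primary outcome event, and for controls the last follow-up".
- **Instrument.** For (a) and (b), an instrumental-variable method will also be explored, "using randomized allocation as the instrumental variable".

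**The concern.** A patient who develops sepsis, kidney injury or gut infarction may be transfused because of it. A model that counts those units as exposure turns a consequence of the event into an apparent cause. The Background section gives apparent harm in observational studies, set against randomized trials that did not show it, as part of the uncertainty behind the trial. A default that can produce such harm from harmless blood is therefore badly placed.

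The trigger adds a second problem. Analysts are likely to find an estimate sensible when it agrees with expectation, and here the bias runs in the direction that earlier observational work would lead one to expect. The estimate-based condition would catch surprising results and let unsurprising biased ones through. That sits poorly with the Discussion, which values these plans because they were fixed before the data were explored.

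Two smaller faults go with it. The fallbacks do not carry over the death component of the outcome. And allocation is offered as an instrument for haemoglobin decline, although allocation also acts through transfusion.

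**Working it through.** **Inputs.** The plan gives no figure for these analyses. Its Sample size section hypothesizes 17% and 11%, so the average event rate is (17 + 11)/2 = 14%, and the target is 2,000 patients. Everything else is assumed: a mean of 2 units before any event, no true effect of units, and the amount of blood given after an event. Pre-event units are taken as Poisson (variance 2) or, more skewed, negative binomial of size 1 (variance 2 + 2²/1 = 6).

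**Closed-form check.** If units are Poisson with mean 2 without an event, and Poisson with mean 2 + e with one (e units follow the event), the ratio of the two probabilities at x units is ((2 + e)/2)^x × exp(−e). The logistic odds ratio per unit is therefore exactly (2 + e)/2:

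- e = 0.5: 2.5/2 = 1.25
- e = 1: 3/2 = 1.50

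For other cases a rough guide is exp(mean difference / variance). If only 10% of event patients receive a mean of 0.5 later units, the mean difference is 0.05, giving exp(0.05/2) = 1.025 or exp(0.05/6) = 1.008. With the skewed distribution and larger differences this guide runs high: exp(0.5/6) = 1.09 and exp(1/6) = 1.18, against simulated values of 1.07 and 1.14.

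**Simulation of the default model** (true odds ratio 1.00; ranges run from the skewed to the Poisson distribution):

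| Blood given after the event | Share of all units | Odds ratio per unit | Tests significant at 5% |
|---|---|---|---|
| 10% of event patients, mean 0.5 | 0.007/2.007 = 0.3% | 1.01–1.03 | close to nominal |
| All event patients, mean 0.5 | 0.07/2.07 = 3.4% | 1.07–1.25 | about 88–100% |
| All event patients, mean 1 | 0.14/2.14 = 6.5% | 1.14–1.50 | 100% |

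The numerators are 0.14 × 0.10 × 0.5 = 0.007, 0.14 × 0.5 = 0.07 and 0.14 × 1 = 0.14 units per patient. Counting only units before the event returns about 1.00 in every row. A separate run with arm means of 1.5 and 2.5 units, adjusted for arm, gave 1.12 (70% significant) when 25% of event patients received a mean of 1 later unit.

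The share column shows why the threshold matters. In the second row only 3.4% of all units follow an event, which could pass as negligible, yet the false association is nearly always significant. Among event patients the share is 0.5/2.5 = 20%, which would not pass. The plan does not say which denominator applies.

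**Event definition.** The stated outcome is the primary outcome or death. Both fallbacks define cases by the primary outcome only. Read literally, a patient who dies without a primary event never becomes a case.

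**Instrument.** Under Methods and Design, allocation is a haemoglobin threshold for transfusion (7.5 or 9 g/dl). Let liberal minus restrictive be dU units and dH g/dl, with direct risk bU per unit and risk bH per 1 g/dl lower haemoglobin.

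- Units: (bU·dU − bH·dH)/dU = bU − bH·dH/dU.
- Haemoglobin: (bH·dH − bU·dU)/dH = bH − bU·dU/dH.

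Take dU = dH = 1 and bH = 0.02 (assumed). With bU = 0.02, both ratios are 0.02 − 0.02 = 0. For units, that 0 is the correct net effect of a unit that harms directly and helps by raising haemoglobin. For haemoglobin it is wrong: lower haemoglobin truly adds 0.02, and the direct effect of transfusion has cancelled it. With bU = 0, the units ratio is −0.02, again the net effect.

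**The case against.** The plan's authors saw the timing problem, said so in print, and named two methods that handle it. The first trigger condition, units given after the event, is a check on the data that does not depend on the estimate. A reader might infer that the time-ordered methods come in only when the result looks implausible. The text does not support that, because the two conditions are joined by an or and offered as examples. Nor does the plan commit to switching; it says alternatives would be considered. These points stand, and they narrow the criticism to the order of the methods, the missing threshold and the second condition.

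The size of the bias also rests wholly on assumed numbers. In the mildest scenario it is trivial, and in the larger ones the first condition might well have been invoked.

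On the instrument, a reader might infer that allocation is invalid for both exposures, or that the two-exposure model is unidentified. Neither reading is supported. If allocation acts only through transfusion, haemoglobin lies downstream of units, and the ratio for units is a legitimate net effect. One binary instrument could not identify two exposures together, but the plan does not say they would be instrumented jointly, and it promises only to explore the method. For haemoglobin decline the objection survives.

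The omission of death could be shorthand in a condensed article. A control who is alive and event-free at the case's event time is legitimate even if that patient dies later. What remains is that the fallback wording does not match the stated outcome.

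**Conclusion.** The point holds in limited form. The default models for units and age of blood admit post-event transfusions. The methods that would remove them are optional and unranked, and one condition for using them depends on the estimate. The fallbacks' event definition omits death, and allocation is not a valid instrument for haemoglobin decline.

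The bias ranges from negligible to large (1.01 to 1.50 per unit when the truth is 1.00), according to how much blood follows events. The documents do not report that quantity, so the calculation shows what the default can do and not what it did. For age of blood the same fault applies, since a later unit can become the oldest one, but its size was not calculated.

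It would be wrong to infer that the trial's main result is touched. These are ancillary observational analyses; the randomized primary comparison and the sample size are unaffected.

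**What to change.** - Make the time-ordered analysis the main one for units and age of blood: time-varying cumulative exposure, or matching to controls still at risk at the case's event time. Count only units before the first event.
- Include death from any cause in the event, to match the stated outcome.
- Report the total-units logistic model as secondary only. Delete the condition about estimates not making sense. With the time-ordered analysis as the default, no threshold for a non-negligible number is needed.
- Drop the instrumental-variable analysis for haemoglobin decline. Keep it for units only if labelled as the net effect per unit, including correction of anaemia, with the assumption stated that allocation acts only through transfusion.

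The cost is a wording change and some programming, using the transfusion and event times that the fallbacks already need. The Discussion says the plan has since been executed, so the change can no longer be prospective. The time-ordered result can still be presented as the main one, with the change of order disclosed.
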